**Figure 4 figure4:**
[figure not shown]
Patient Activities Flow Diagram.

### Clinician Study Activities and Quantitative Data Collection

All enrolled clinicians will complete an electronic baseline survey and exit survey about their scope of contraceptive practice and knowledge of contraceptive care in the context of diabetes, hypertension, migraine headaches, and multiple risk factors for cardiovascular disease (common clinical scenarios). Clinicians in both arms will receive a web link to a video that reviews “What to Expect” regarding study activities. Only clinicians in the intervention arm will receive web links to the MHMC tool and a brief video that reviews how to navigate the tool’s features. After each clinic visit with an enrolled patient, clinicians will complete a 3-minute postvisit survey. The study team will invite approximately 30 clinicians at the end of the study to do an optional 1-hour qualitative exit interview by phone or videoconference (refer to “Qualitative Data Collection and Sampling Considerations” section). Clinicians will receive up to US $75 in cash remuneration for study activities (Figure 5).

**Figure 5 figure5:**
[figure not shown]
Clinician Activities Flow Diagram.

### Clinic Study Activities and Quantitative Data Collection

After patients exit the study, the Clinic Team will conduct an EMR review of each enrolled patient’s chart to corroborate 3-month study outcomes, including contraceptive use (contraceptive prescriptions, IUD, or implant insertions) or plans to obtain IUDs, implants, or tubal surgery for themselves or vasectomy for their partners (scheduled visits and referrals).

### Qualitative Data Collection and Sampling Considerations

To achieve the qualitative and mixed methods part of Aim 2, we will purposefully sample patients [40] across US MEC Categories 1, 2, 3, and 4). We will oversample patients who report the use of Category 3 to understand factors that led to the use of a method that should be avoided except under special circumstances. As an example, if a patient with well-controlled hypertension reports using a combined hormonal pill (Category 3 use), does this reflect oversight or unawareness of the risks by the patient, the clinician, or both? Or did the patient and clinician carefully review the pros and cons in light of the patient’s other comorbidities, age, and tolerance for risk? To what extent, if at all, did use of the intervention contribute to this process? While US MEC Categories will primarily drive qualitative sampling, we will also seek perspectives across a range of chronic conditions (cardiovascular, endocrine, psychiatric, neurologic, and autoimmune) and contraceptive method types whenever feasible, and across both arms. We also aim to purposefully sample clinicians who provided care to the index patients who agree to be interviewed, which will allow for comparison of patient and clinician perspectives on the clinic discussion and decision-making process.

To prevent the risk of affecting participant behavior or survey responses, we will conduct patient interviews right after they exit the study at 3 months and clinician interviews at the end of their clinic’s trial participation. A trained qualitative RA will conduct 30- to 60-minute interviews with participants over the phone or via videoconference. All audio and video recordings will be uploaded immediately to a secure cloud server. A professional transcriber will transcribe exit interviews verbatim. Personal identifiers for people and places will be removed and replaced with pseudonyms.

Theoretical saturation refers to the point at which data analysis reveals no further significant findings relevant to the research aims and is commonly used in qualitative research to determine sample sizes [41]. Based on our exit interviews from our pilot study and best practices in qualitative sampling [41,42], we anticipate that interviewing 2 patients and 2 clinicians per clinic (about 60 interviews total, 30 patients and 30 clinicians) will provide high-quality data to achieve theoretical saturation. Upon reaching theoretical saturation, we will stop collecting interview data.

### Power and Quantitative Sample Size

The primary outcome is the proportion of participants reporting contraceptive nonuse at 3 months. Based on national estimates [10,11,43,44] and our screening protocol, we anticipate 30% (217/726) of participants at baseline will report contraceptive nonuse. A previous cluster RCT of a contraceptive decision tool in outpatient clinics found a clinic-level intracluster correlation (ICC) of 0.02 [16]. We conservatively estimate an ICC of 0.05. Prior studies have estimated ICCs generally <0.04 for patient-reported outcomes in maternal health and sexual behavior among reproductive-aged women [45-47]. To reduce our estimated ICC, we have taken several precautions. At the design level, we have defined clinic, patient, and clinician eligibility criteria to reduce heterogeneity and variance in estimates [48]. At the analysis level, we will conduct regression adjustment for key covariates [48]. To detect a difference of 20% in the proportion of contraceptive nonuse between the intervention arm and the control arm at 3 months, an effect size consistent with that of prior contraceptive trials [20,49,50], we will need to enroll 14 clinics (7 in each arm) and 45 participants in each clinic. Assuming an attrition rate of 15%, our enrollment goal is 726 patients (363 patients in each arm). We anticipate that we will enroll 5-10 clinicians per clinic, for a maximum total of about 140 clinicians. The allocation ratio will be 1:1 with attention to the balance of obstetrics and gynecology clinics in each arm, which will mitigate the impact of unequal distribution of sites that provide higher volume or scope of contraceptive services.

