It is also important to bear in mind that most people with health conditions are medically eligible to use most methods [13]; that is, the proven or theoretical benefits of using a specific method generally outweigh any risks in the majority of cases. However, fear of side effects and health concerns are among the most common reasons cited for not using the most preferred method or not using any method among US contraceptive candidates in a nationally representative survey [14]. Contraceptive nonuse, defined as not using any method despite wanting to prevent pregnancy, is associated with the highest risk of unplanned pregnancy [15]. The use of any method reduces the risk of pregnancy by 70%-99.9%, depending on the method type [15]. Patients should receive accurate and balanced information about contraceptive-related health risks, including cases where there is no known risk, to prevent unnecessary avoidance of otherwise safe methods.

In prior randomized controlled trials (RCTs), contraceptive decision tools have been associated with improved patient contraceptive knowledge [16,17], improved quality of contraceptive care experience [16], reduced contraceptive decisional conflict [16], or increased use of prescription contraception [17,18], while others showed no significant differences in outcomes [19-21]. These trials primarily enrolled healthy young adults or adolescents [16,19,20] and did not address clinician knowledge regarding contraceptive use for patients with health conditions.

However, evidence-based clinical guidelines for contraceptive use by people with health conditions do exist. The Centers for Disease Control and Prevention (CDC) United States Medical Eligibility Criteria (US MEC) summarizes evidence-based and expert-informed recommendations for the safe use of contraceptive methods in the context of more than 60 health conditions and characteristics [13]. To distill the 124-page document for clinical use, the US MEC content is available as a free smartphone app and a downloadable color-coded PDF chart summary [22,23]. However, studies show that the US MEC is underused by clinicians, particularly in primary care [24-27] settings. A decision tool that engages both patients and their clinicians is a novel yet unexplored approach to promote informed contraceptive decision-making and use in the context of health conditions.

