Eligible patients must (1) be aged 18-49 years; (2) be assigned female sex at birth (regardless of gender identity); (3) be able to read in English; (4) have access to a mobile phone, computer, or tablet with internet capabilities; (5) be fertile (have an intact uterus and at least 1 ovary, be premenopausal, have never had permanent contraception surgery, and have no known medical reasons for current infertility, such as use of ovarian suppression medications); (6) have at least 1 index health condition, take an eligible medication, or both (Multimedia Appendix 1; (7) not be currently pregnant; and (8) have a desire to start, switch, or add a contraceptive method for the purpose of preventing pregnancy. Patient exclusion criteria include patients who expect to try getting pregnant in the next 12 months or are presumed infertile for any reason (eg, postmenopausal, hysterectomy, or chemotherapy). During our recruitment process, we explicitly clarify to clinics, clinicians, and patients that transgender patients and postpartum patients are eligible for the trial as long as they meet all other eligibility criteria noted above. Of note, we are developing a Spanish version of the MHMC tool and anticipate expanding eligibility to Spanish-speaking patients in 2026.

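### The enrolment goal of 726 multiplies by 1.15 instead of dividing by 0.85, so 15% attrition leaves about 617 participants, not the required 630; the effect on power is negligible

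*Protocol article*

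**What the plan says.** All the figures are in the protocol article, section Power and Quantitative Sample Size.

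- Requirement: "we will need to enroll 14 clinics (7 in each arm) and 45 participants in each clinic".
- Attrition and goal: "Assuming an attrition rate of 15%, our enrollment goal is 726 patients (363 patients in each arm".
- Clustering: "We conservatively estimate an ICC of 0.05".
- Target effect: "To detect a difference of 20% in the proportion of contraceptive nonuse between the intervention arm and the control arm at 3 months".
- The only nonuse rate given: "we anticipate 30% (217/726) of participants at baseline will report contraceptive nonuse".

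The eligibility criteria add that every patient must "have a desire to start, switch, or add a contraceptive method for the purpose of preventing pregnancy".

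**The concern.** A reader takes the paragraph to mean that 726 enrolled, less 15%, gives the 630 on which the design rests. It does not. Inflating by 1 + d in place of 1/(1 − d) always falls short, and the published attrition allowance is then larger than the one the goal provides. Whoever monitors retention against 15% would believe the trial was still on its planned size when it was already under it.

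A second matter in the same paragraph bears on how the target is read. The outcome is nonuse at 3 months, but the one rate shown beside the 20% difference describes patients at entry. All of them want to start, switch or add a method, and control patients also attend a visit for usual contraceptive care. Their nonuse at 3 months may therefore be lower than at baseline, and the paragraph does not say what level was assumed.

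**Working it through.** **Inputs, all from Power and Quantitative Sample Size:** 7 clinics per arm, 45 participants per clinic, attrition d = 0.15, goal 726 (363 per arm), intracluster correlation 0.05.

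**1. Reproducing 726**
- Required: 14 × 45 = 630, or 315 per arm.
- Multiplying by 1 + d: 315 × 1.15 = 362.25, rounded up to 363; 2 × 363 = 726. This matches the stated goal exactly.

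**2. The correct inflation**
- Dividing by 1 − d: 315 / 0.85 = 370.6, rounded up to 371 per arm; 2 × 371 = 742, or 53 per clinic.
- Difference in enrolment: 742 − 726 = 16, which is 2.2% of 726.

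**3. What 726 delivers**
- 726 × 0.85 = 617.1, or 617.1 / 14 = 44.1 per clinic.
- Shortfall against 630: about 13 completers (2.1%).
- Loss tolerated before falling below 630: 1 − 630/726 = 13.2%.

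**4. Effect on power**

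The article does not print alpha or power. I assume a two-sided 5% level and do not raise their absence, since the full protocol may hold them. The design effect is 1 + (m − 1) × 0.05, and the effective number per arm is 7m divided by it.
- m = 45: design effect 3.20; effective n = 315 / 3.20 = 98.4 per arm.
- m = 44.1: design effect 3.154; effective n = 308.55 / 3.154 = 97.8 per arm.

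| Comparison | Method | m = 45 | m = 44.1 |
|---|---|---|---|
| 30% v 10% | normal approximation | 94.5% | 94.4% |
| 30% v 10% | t, 12 df | 91.3% | 91.2% |
| 50% v 30% | normal approximation | 82.2% | 82.0% |
| 50% v 30% | t, 12 df | 76.6% | 76.3% |

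The loss is 0.1 to 0.3 points. With 14 clinics and this correlation, precision is governed mainly by the number of clinics, so one patient fewer per clinic hardly matters.

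**5. Whether 7 × 45 follows from a 20-point difference**

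At 80% power (assumed), clinics per arm = n per arm for independent patients × 3.20 / 45.
- 60% v 40%, where the variance is largest: 97 × 3.20 / 45 = 6.9, so 7.
- 50% v 30%: 93 × 3.20 / 45 = 6.6, so 7.
- 30% v 10%: 62 × 3.20 / 45 = 4.4, so 5.

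The stated design is reproduced at or near maximum variance and does not need 30% as its control rate.

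**6. Room for a 20-point reduction**

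A reduction of 20 points needs a control rate of at least 20%. As an illustration only, let q be the share of baseline nonusers still not using a method at 3 months, and suppose 5% of baseline users stop. Control nonuse is then 0.30q + 0.70 × 0.05.
- q = 50%: 0.150 + 0.035 = 18.5%, and a 20-point fall is impossible.
- Control nonuse exceeds 20% only if q > (0.200 − 0.035) / 0.30 = 55%.

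Neither q nor the 5% is in the document.

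**The case against.** The best defence is that the slip has no practical consequence: 16 patients, 13 completers and a few tenths of a point of power. That stands, and it sets the severity. It does not make the printed figures agree, because 15% off 726 is not 630. Nor does it help to read 45 as the number enrolled per clinic, since 14 × 45 is then still 630 and not 726.

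The paragraph may tempt a reader to go further in five ways. The document supports none of them.

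- *The 20% is measured against baseline.* The text places the difference between the arms at 3 months, and 30% is never called the control rate.
- *The inputs do not yield 7 clinics of 45.* They do for a 20-point difference near maximum variance. Sizing there is conservative: if the control rate is 30%, a 20-point difference has more power than planned.
- *There is no attrition allowance.* There is one, of 13.2%.
- *The 20% might be relative.* A relative 20% from 30% (30% v 24%) would have only about 15% power with 7 × 45, so the design was plainly not sized for it. A difference in a proportion ordinarily reads as absolute.
- *Reference 20 is misused.* It is cited in support of the effect size, and also in the Background and Rationale section, "while others showed no significant differences in outcomes [19-21". A non-significant trial can still show or be planned on a difference of that size, and the source is not available here.

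It is also fair to say that a fall in control nonuse is conjecture. It remains a reason to state the assumed 3-month rate, but it is not evidence of an error.

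**Conclusion.** The attrition arithmetic is wrong, and this follows from the document's own figures without outside assumptions: 726 is 2 × 363, from 315 × 1.15, and 15% loss leaves about 617 (44 per clinic) instead of 630. The goal supports a 13.2% allowance, and a true 15% allowance needs 742. The loss of power, 0.1 to 0.3 points, rests on the planned correlation of 0.05, equal clinic sizes and an assumed two-sided 5% test. Severity is minor.

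On the effect size, the supportable statement is limited. The one nonuse rate in the paragraph is a baseline rate, the target is a difference at 3 months, and the 3-month control rate behind it is not shown. Whether 20 points is attainable depends on that rate staying at or above 20%, which the document neither establishes nor contradicts.

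**What to change.** Keep 726 and correct the sentence in one of two equivalent ways: about 617 evaluable (44 per clinic) at 15% attrition, or 630 evaluable with a 13% attrition allowance. If the sponsor prefers to hold both 630 and 15%, the goal becomes 742 (371 per arm, 53 per clinic). In the same edit, state the control-arm nonuse assumed at 3 months, identify 30% as the baseline figure only, and note that the 20-point target presupposes control nonuse of at least 20%.

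Keeping 726 costs wording only, with slightly less favourable printed figures. Moving to 742 costs 16 more patients for almost no gain in power, so restating is the better choice.

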### Randomization Process, Allocation Concealment, and Blinding

To avoid potential contamination across providers and patients, we will randomize by clinic site.

Clinics will be randomized in even-numbered blocks (2,4) to ensure balanced allocation of group conditions. The lead biostatistician (AS) will generate the allocation sequence and assign clinics to the intervention arm or control arm. Due to the cluster-randomized design, allocation concealment is impractical, and it will not be possible to blind patients or clinicians. The study team will remain blinded to the group assignment when evaluating outcomes.

### Quantitative Outcomes and Analysis

The primary outcome is contraceptive nonuse at 3 months per patient self-report, consistent with prior contraceptive studies [10,51,52]. Individual contraceptive nonuse will be modeled as a binary outcome. We will use mixed-effects nested logistic regression to assess differences in 3-month outcomes between the study arms. The model will include an arm assignment categorical covariate and will be adjusted using patient-level covariates (baseline contraceptive nonuse, education, race, ethnicity, and parity) and clinician-level covariates (self-reported experience with contraceptive care and specialty type). Random intercepts for the clinic and for clinicians nested within the clinic will account for the clustering. Secondary analyses of contraceptive nonuse will include the same model with 1-month data and a subgroup analysis that only includes patients at risk for pregnancy, that is, those who report penile-vaginal sexual activity at 1 month and 3 months.

The secondary quantitative outcome is patient-reported contraceptive method use as classified by the US MEC. We will summarize US MEC Categories 1, 2, 3, or 4 among patients who report contraceptive use at 1 month and at 3 months with descriptive statistics. Chi-square tests will be calculated to compare frequencies between the intervention group and the usual care group.

The exploratory outcomes are hypothesized mediators of the intervention effect on the primary and secondary outcomes. First, contraceptive decisional conflict will be assessed with the DCS, a 16-item validated scale with 4 subscales [29] (0=no conflict; 100=greatest conflict). We slightly modified the wording of DCS items, when appropriate, to reflect contraceptive decisions rather than generic health decisions. Second, we will assess patient-reported quality of interaction with their contraceptive provider via the IQFP [30]. The IQFP contains 11 items that are assigned a score of 1-5 (1=poor, 2=fair, 3=good, 4=very good, and 5=excellent) by the patient to assess their clinician’s shared decision-making and interpersonal skills (total scores ranged from 11 to 55). We will conduct a mediation analysis as described by Baron and Kenny [53] with two models: (1) a logistic regression of the mediator (ie, DCS or IQFS, dichotomized) as a function of the primary outcome (contraceptive nonuse at 3 months), with a covariate for intervention versus control group, and (2) a logistic regression of the primary outcome (contraceptive nonuse at 3 months), adjusting for both the mediator (ie, DCS or IQFPS, dichotomized) and intervention versus usual care group.

We will conduct descriptive analyses on other patient, clinician, and clinic-level exploratory measures and statistical comparison tests as appropriate (eg, chi-square, Fisher exact, and *t* tests).

Patient-level measures: We will categorize patient-reported contraceptive use by method type and method effectiveness (highly effective, moderately effective, and less effective) to enable comparison with other studies. Patients will be asked to assess 6 knowledge questions regarding contraceptive safety (true, false, or I don’t know) at baseline, postdecision tool use (for intervention arm only), and postclinic visit. Patients will be instructed to report any pregnancies that occur during the study and at 1 month and 3 months. For any pregnancies reported, patients will be asked to describe their pregnancy intentions at the time of pregnancy using a standardized single item [54]. Patients who are still pregnant at the time of reporting will exit the study and seek follow-up care; they may contribute data up until the point of study exit.Clinician-level measures: We will assess clinician knowledge of the US MEC Guidelines at baseline and exit surveys with 5-point Likert-scale items regarding 4 clinical scenarios.Clinic-level outcomes: RE-AIM is an evaluation framework to assess an intervention’s potential to be translated to real-world settings [35]. We will assess each dimension of RE-AIM with quantitative data, qualitative data, or both:Reach: We will collect demographics of participants offered the intervention and those who used the intervention, and these will be compared with those of the usual contraceptive care arm, as well as the general US population at risk for unplanned pregnancy (quantitative).Efficacy: We will examine the primary outcome of contraceptive nonuse (quantitative) in the context of patient and clinician perspectives on the intervention’s impact (qualitative).Adoption: We will report the percentage of patients and clinicians in the intervention arm who used the decision tool intervention.Implementation: We will report patient and clinician fidelity to the intervention and what natural adaptations were made (quantitative and qualitative).Maintenance: We will summarize patient- and clinician-reported facilitators, barriers, and suggested changes to sustain use of the intervention in clinical practice beyond the clinical trial (qualitative).

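### With 14 clinics, the primary mixed logistic model needs a stated small-sample method: the usual maximum-likelihood Wald test would reject a true null about 8% to 11% of the time, not 5%

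*Protocol article*

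**What the plan says.** The Quantitative Outcomes and Analysis section defines the primary analysis: "We will use mixed-effects nested logistic regression to assess differences in 3-month outcomes between the study arms". The model has an arm term, patient-level covariates (including baseline nonuse) and "clinician-level covariates (self-reported experience with contraceptive care and specialty type". On clustering it says: "Random intercepts for the clinic and for clinicians nested within the clinic will account for the clustering". It does not give the estimation method, the test of the arm effect, the degrees of freedom or the significance level.

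The Power and Quantitative Sample Size section fixes the design: "we will need to enroll 14 clinics (7 in each arm) and 45 participants in each clinic". On the correlation it says "We conservatively estimate an ICC of 0.05"; the earlier trial it relies on "found a clinic-level intracluster correlation (ICC) of 0.02". On the event rate, "we anticipate 30% (217/726) of participants at baseline will report contraceptive nonuse". The randomisation section confirms that the clinic is the unit of allocation.

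**The concern.** Arm is assigned to clinics, so the evidence on the arm effect comes from comparing 7 clinic means with 7 others. The between-clinic variance is estimated from 14 clinics. Maximum likelihood underestimates it, and a normal reference distribution ignores the uncertainty in the estimate. Random intercepts put the clustering into the model, but they do not by themselves correct either fault.

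Covariates that vary mainly between clinics use up further degrees of freedom. Specialty is probably one of these, since the Abstract describes clinics that specialise in primary care or in obstetrics and gynecology. At stake are the false-positive rate of the trial's single primary test and the coverage of the interval for the odds ratio.

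**Working it through.** **Inputs from the article.** 14 clinics, 7 per arm, 45 patients per clinic, planning ICC 0.05, earlier-trial ICC 0.02, baseline nonuse 30%, 5 to 10 clinicians per clinic, difference to detect 20 percentage points, attrition 15%.

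**Assumptions.** Two-sided 5%, equal clinic sizes, null event rate 30% (20% as sensitivity), specialty constant within clinic.

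**The plan's own figures.** 7 × 45 = 315 per arm. 315 × 1.15 = 362.25, so 363 per arm and 726 in total, as stated. The design effect is 1 + 44 × 0.05 = 3.2. The two 3-month rates are not stated. At 80% power, 50% vs 30% needs 93 × 3.2 / 45 = 6.6 clinics per arm, and 60% vs 40% needs 97 × 3.2 / 45 = 6.9. Both round to 7, so the design is reproduced under those rates.

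**Type I error by approximation.** Suppose the statistic follows t on 14 − k degrees of freedom, where k is the number of clinic-level coefficients including the intercept, and maximum likelihood shrinks the variance by (14 − k)/14.
- Normal reference only, no shrinkage, k = 2: P(|t12| > 1.96) = 7.4%.
- Maximum-likelihood Wald z, arm only, k = 2: P(|t12| > 1.96 × √(12/14)) = 9.5%.
- With one clinic-level covariate, k = 3: P(|t11| > 1.96 × √(11/14)) = 11.0%.

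This treats all the variance of a clinic mean as between-clinic variance, so it is an upper guide rather than an exact value.

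**Type I error by simulation.** Data were generated under the null with 14 clinics of 45. The random-intercept logistic model was fitted by maximum likelihood with Gauss-Hermite quadrature. There were 5,000 runs per setting for the clinic-intercept model and 2,000 for the nested clinic and clinician model with 7 clinicians per clinic. The Monte Carlo standard error is about 0.3 to 0.4 points for 5,000 runs and 0.7 points for 2,000.

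Rejection rates at ICC 0.05:

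| Test | Arm only | One clinic-level covariate | Two |
|---|---|---|---|
| Wald z, clinic intercept | 8.0–8.7% | 9.8–10.9% | 10.9–12.1% |
| Wald z, clinic and clinician intercepts | 8.1–9.5% | 10.1–11.0% | not run |
| Likelihood ratio | 6.4–7.2% | 8.1–9.1% | 9.1–10.4% |
| Wald with between-clinic t df | 5.5–6.0% | 6.3–7.7% | 6.7–8.4% |

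An unadjusted t test on clinic proportions (12 df) gave 4.4–5.5% across these settings. At ICC 0.02, Wald z gave 7.0–10.5%, depending on event rate and covariates.

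**Interval width.** The 12-df critical value is 2.179, against 1.960. The ratio is 1.11 from the reference distribution alone. Undoing the variance shrinkage as well gives 1.11 × √(14/12) = 1.20, by the same upper-guide approximation.

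**Power at ICC 0.05, 315 per arm.** The effective n is 315 / 3.2 = 98.4 per arm. For 50% vs 30%, the unpooled standard error is √((0.25 + 0.21)/98.4) = 0.0684, and the pooled one under the null is √(2 × 0.4 × 0.6/98.4) = 0.0698.
- Normal: Φ((0.20 − 1.96 × 0.0698)/0.0684) = 82%.
- Noncentral t on 12 df, noncentrality 0.20/0.0684 = 2.93: 77%.
- For 30% vs 10%, the same steps give 94.5% and 91%.

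With the unpooled standard error in both calculations, the normal figures are 83% and 95%, so the loss is about 4 to 7 points.

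**The case against.** The strongest objection is that this is silence rather than error. The article does not say maximum likelihood, does not say Wald z and does not rule out a small-sample correction. It condenses a fuller protocol, and degrees of freedom are ordinary content for an analysis plan that is not shown. This stands as far as it goes. A reader might infer that the trial has decided against small-sample inference, or that its false-positive rate will be 9% to 11%. The article supports neither inference.

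The size also depends on choices that are left open. With arm only, a likelihood-ratio test gives about 6.5% to 7%, and t degrees of freedom on the same fit about 6%. The ICC of 0.05 is described as conservative. However, at ICC 0.02 Wald z still rejects 7% or more, so a lower correlation does not remove the problem.

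What remains is that the article does more than leave a gap. It specifies the model in detail and presents the random intercepts as what accounts for the clustering. With that model fitted by maximum likelihood, neither usual test held 5% at the planning ICC, and nothing in the article corrects this. If the full analysis plan already names a valid method, the sponsor need only confirm it.

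**Conclusion.** The point holds in conditional form. If the arm effect is tested by an uncorrected maximum-likelihood Wald z, type I error at ICC 0.05 is about 8% to 9.5% with arm only and about 10% to 11% with a clinic-level covariate such as specialty. That is 1.6 to 2.2 times the nominal 5%, and the odds-ratio interval is too narrow. A likelihood-ratio test reduces the excess to about 6.5% to 9% but does not remove it.

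This rests on a two-sided 5% test, equal clinics of 45, null nonuse of 20% to 30%, and specialty constant within clinic. If specialty varies within clinics, the arm-only range is the better guide. The power figures rest on assumed arm rates.

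**What to change.** Keep the mixed logistic model for estimation. State that the primary p-value and confidence interval come from a method valid with few clusters. The preferred choice is a clinic-level permutation test that respects the randomisation scheme, or a t test on covariate-adjusted clinic summaries with 12 degrees of freedom, reduced for any clinic-level covariate. The unadjusted version of the t test held its level in the simulations; the adjusted and permutation versions were not run.

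Restricted pseudo-likelihood with Kenward-Roger or between-within degrees of freedom is an alternative, also not simulated here. Simply attaching t degrees of freedom to the maximum-likelihood fit is not enough, since it leaves about 5.5% to 8%. State the significance level and the two assumed arm rates, and use the same reference distribution in the power calculation.

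The cost is a few sentences, fixed before any outcome comparison by arm. Intervals widen by about 11%, up to about 20%, relative to the uncorrected ones. At ICC 0.05, power falls from about 82% to 77% if the rates are 50% vs 30%, or from about 94.5% to 91% if they are 30% vs 10%. Under the first pair, the sponsor should decide whether 77% is acceptable with 14 clinics.
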